#### Resource utilization outcomes

##### Sleep interference

The Medical Outcomes Study (MOS) sleep scale will be used to assess the quality and quantity of sleep. This questionnaire has 12 items that assess the key constructs of sleep. It is a self-administered questionnaire in which patients are asked to recall sleep-related activities over the past four weeks. There is scoring in six domains: sleep disturbance (4 items), snoring (1 item), awakening with shortness of breath or a headache (1 item), quantity of sleep (1 item), optimal sleep (1 item), sleep adequacy (2 items), and daytime somnolence (3 items) [47].

### International physical activity questionnaire-short form (IPAQ-SF)

The IPAW-SF will be used to assess physical activity in multiple domains, including leisure time, domestic and gardening (yard) activities, and work-related and transportation-related activities. The items in the questionnaire are structured to provide separate scores for walking, moderate-intensity activity, and vigorous-intensity activity, as well as a combined total score that describes overall level of activity. Computation of the total score requires summation of the duration (min) and frequency (days) of walking, moderate-intensity activity, and vigorous-intensity activity. This questionnaire is available in multiple languages, and a validated Spanish version will be used [48].

### Modified Borg scale (MBS)

The MBS is a frequently used quantitative measure of perceived exertion during physical activity. A single question asks the patient to rate the impression of exercise intensity on a scale of 0 (not at all) to 10 (maximal) [49].

### Baseline data collection

To assess the comparability of the study groups, baseline demographic and medical information will be collected from all medical records at the time of enrollment. The clinical history of the mother will include date of birth, socio-economic status, parity, date of last menstrual period, estimated date of partum, risk factors during pregnancy, clinical antecedents, surgery and personal obstetric data, health-related habits, and preference for analgesia during delivery.

### Blinding

The nature of this study did not allow blinding of women and midwifes to group allocation. However, the outcome assessments will be conducted by external personnel (not involved in the study) who will be blinded to allocation. To avoid a potential Hawthorne effect, in which women in the intervention group change their behaviors (e.g. avoid use of epidural analgesia) because they know they are being observed, the women were not specifically informed that use of epidural analgesia was the main outcome measure, although they were completely informed of all the aims of the study. The statistician and data entry staff were also blinded to allocations.

### Statistical analysis

We will test for significant baseline differences in the control and intervention arms by use of descriptive analysis, with continuous variables summarized by means and standard deviations if they have normal distributions, and by medians and 25th and 75th percentiles if they have non-normal distributions.

All analyses of the effectiveness and cost-effectiveness will consider the intention-to-treat population (i.e. all randomized patients, regardless of participation in any intervention session). This approach reduces bias that may occur when participants not receiving an assigned intervention are excluded from the analysis. All tests will be two-sided, and an α-value of 0.05 will be considered statistically significant.

We will compare the proportions of women in each arm who use epidural analgesia during labor, in which the null hypothesis is no difference between the groups. We will use the Chi-squared test in bivariate analysis, and will adjust for potential confounders (if any) using a logistic regression model.

We will estimate the relative and absolute risk reduction and the number needed to treat (NNT). All estimates will include 95% confidence intervals. The NNT will be calculated as the reciprocal of the difference between the proportion of women who required epidural analgesia during labor in the intervention and control arms.

The secondary measures of effectiveness, such as reduction of instrumental delivery, reduction of Caesarean section, and post-partum depression, will be evaluated by a Chi-squared test. We will use the Mann-Whitney U test to determine if there is a statistically significant reduction of pain during labor using a VAS.

The health economic analysis will be performed by calculating the incremental cost-effectiveness ratio (ICER) at 4 weeks from delivery. We will systematically collect data on use of all resources, including inpatient care, consultations with healthcare providers, use of drugs, and laboratory tests. To measure these effects, the EQ-5D scores will be used, and quality-adjusted life years (QALYs) will be determined. The ICER will be calculated as the difference in the mean costs of the 2 groups (C_1_ – C_T_) divided by difference in the mean effects of the 2 groups (E_1_ – E_T_):$$ ICER=\frac{\overline{C_1}-\overline{C_T}}{\overline{E_1}-\overline{E_T}} $$

A nonparametric bootstrap procedure will be used to perform the uncertainty analysis for the ICER. This procedure considers the skewness of cost data, and the covariance of costs and QALYs. To control for possible confounding and to account for clustering, an alternative procedure (Net-Benefit Regression) will also be used. Cost-effectiveness acceptability curves will be presented to show statistical uncertainty. We will determine the safety of all interventions on the “safety population” and use “per protocol analysis” to compare adverse events of patients using the Chi- squared test.

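### Adjustment of the primary outcome is left to whatever confounders are found, neither the crude nor the adjusted result is named primary, and parity and analgesia preference have no assured role

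*Protocol article*

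**What the plan says.** All of this is in the Protocol article.

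- **Statistical analysis, first paragraph:** "We will test for significant baseline differences in the control and intervention arms by use of descriptive analysis". The sentence announces a significance test and then describes summary statistics.
- **Statistical analysis, significance level:** "All tests will be two-sided, and an α-value of 0.05 will be considered statistically significant".
- **Statistical analysis, primary outcome:** the arms are compared by Chi-squared test, and the investigators "will adjust for potential confounders (if any) using a logistic regression model". Relative and absolute risk reduction and the number needed to treat follow, all with 95% confidence intervals. The number needed to treat is defined from the two arm proportions, so it is a crude quantity.
- **Baseline data collection:** the enrolment record includes "date of birth, socio-economic status, parity, date of last menstrual period" and, at the end of the list, "health-related habits, and preference for analgesia during delivery". The stated purpose is to judge whether the groups are comparable; no analysis role is given.
- **Sample size:** refers to a primary analysis in the intention-to-treat population without saying which analysis that is.
- **Procedures, recruitment, randomization:** 1:1 allocation in blocks of six, with no stratification factor stated.
- **Blinding:** the statistician is blinded to allocation.

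**The concern.** In a randomised trial, baseline differences between arms arise by chance, so a significance test on them answers no useful question. It is also a poor guide to adjustment. What matters is how strongly a variable predicts the outcome, not whether its imbalance reaches p < 0.05.

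The words in brackets, (if any), make the adjustment conditional on what the data show. Two results for the primary outcome can then exist, a crude one and an adjusted one whose covariates were chosen after the data were seen, and no rule says which is the trial's answer.

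Parity and preference for analgesia are the obvious candidates for adjustment. Whether to have an epidural is in part the woman's choice; the Blinding section itself worries that women might change their behaviour in this respect. Nothing stated in the randomisation balances either variable, and nothing in the analysis ensures that either is used.

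**Working it through.** The protocol gives no figure for this point to reproduce. The check asks what an open adjustment rule costs compared with a fixed one.

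**Inputs from the Protocol article.** Control rate 61%; a 20% reduction, not stated to be absolute (61% to 41%) or relative (0.8 × 61% = 48.8%); 160 per arm; 15% loss; two-sided α of 0.05. Women with an outcome: 160 × 0.85 = 136 per arm.

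**Assumptions, not in the document.** Two independent binary predictors, each with 50% prevalence and an odds ratio (OR) of 2, 3 or 5 for epidural use; eight further covariates unrelated to outcome; selection of any covariate whose baseline test gives p < 0.05. The protocol does not state that selection rule. It is used because no other criterion is given.

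**Step 1: how often a baseline-significance rule picks the useful covariates.** Under randomisation each test is positive with probability 0.05.
- A given predictor is picked in about 5% of trials and unused in about 95% (simulated: picked in 3.8% to 5.7%).
- Both are picked in 0.05² = 0.25% (simulated: 0.1% to 0.3%).
- At least one of ten is picked in 1 − 0.95¹⁰ = 40% (simulated: 36% to 39%). Some adjustment would therefore be common, but seldom for the variables that matter.

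**Step 2: power and type I error.** The model is logit P(epidural) = a + b·arm + ln(OR)·(Z₁ + Z₂), with a and b solved to give the stated arm rates; 3,000 runs per setting. Where the rule picked nothing, the Chi-squared result was used.

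| Setting | OR | Crude | Selected covariates | Both predictors pre-specified |
|---|---|---|---|---|
| Power, 61% vs 41% | 2 | 90.7% | 90.7% | 93.0% |
| | 3 | 90.5% | 90.7% | 94.2% |
| | 5 | 91.5% | 92.4% | 96.5% |
| Power, 61% vs 48.8% | 2 | 52.6% | 52.4% | 55.7% |
| | 3 | 51.7% | 51.2% | 57.5% |
| | 5 | 51.1% | 50.8% | 61.3% |
| Type I error | 2 | 5.6% | 5.5% | 5.7% |
| | 3 | 5.8% | 5.3% | 5.3% |
| | 5 | 5.0% | 4.5% | 4.8% |

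The crude column agrees with the usual two-proportion formula at 136 per arm (91.4% and 52.5%). Simulation error is about √(0.05 × 0.95 / 3000) = 0.4 points for the type I rates and √(0.5 × 0.5 / 3000) = 0.9 points for power near 50%.

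Gain of pre-specified over crude: 93.0 − 90.7 = 2.3 to 96.5 − 91.5 = 5.0 points at 61% vs 41%; 55.7 − 52.6 = 3.1 to 61.3 − 51.1 = 10.2 points at 61% vs 48.8%. The selection rule recovers almost none of this.

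**Step 3: reporting the more favourable result.** Taking the smaller p-value of crude and selected-adjusted gives type I error of 6.0%, 6.1% and 5.4% for OR 2, 3 and 5, against 5.6%, 5.8% and 5.0% for crude alone in the same runs. Taking the smaller of crude and predictor-adjusted gives 6.7%, 7.6% and 7.0%.

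**Step 4: an illustration of chance imbalance.** Suppose half the women prefer an epidural, and 80% of those who do use one against 42% of the others (average 61%). The implied OR is (0.80/0.20)/(0.42/0.58) = 5.5, just above the range used in Step 2. A 10-point imbalance in preference shifts the crude difference by 0.10 × 0.38 = 3.8 points. A significant imbalance needs 1.96 × √(2 × 0.25/136) = 11.9 points, so a p < 0.05 rule would pass over it. The standard error of the crude difference is √[(0.61 × 0.39 + 0.41 × 0.59)/136] = 5.9 points, so the shift is 3.8/5.9 = 0.64 standard errors. An imbalance of 10 points or more in either direction occurs in about 10% of trials.

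**The case against.** The strongest reply is that the plan contains a valid, fixed primary comparison. The arm proportions are compared by Chi-squared test and the number needed to treat comes from those proportions. This is a condensed article, and the covariate list commonly sits in an analysis plan that is not shown. Much of this stands, and it rules out several stronger readings.

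- A reader might infer that confounders are, by rule, the variables significant at baseline. The two sentences stand in different paragraphs and no link is stated. It is the only criterion in sight, but it remains an inference.
- A reader might infer that the primary estimate itself depends on the data. Only the logistic model does; the crude results are fixed in advance.
- A reader might call the 3.8-point shift bias. It is chance imbalance. The crude difference is unbiased over randomisations and its confidence interval already allows for such imbalance.
- A reader might see a clash between an odds ratio and the planned risk measures. The protocol never promises an odds ratio as the reported effect, and a logistic model can yield risk differences. No error is shown here.
- A reader might call parity and preference strong predictors. The document gives no strength for either; OR 2 to 5 is an assumption.

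Blinding of the statistician limits steering towards an arm, but it neither fixes the covariates nor names the primary result. The article also goes beyond leaving detail to another document: it commits to testing randomised arms for baseline differences, makes adjustment conditional, and sets two analyses of the primary outcome side by side without ranking them. Those points survive.

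**Conclusion.** The concern holds in a limited form. The adjusted model is left dependent on the data, the primary analysis is not identified, and two plausible predictors already collected may go unused. The trial's validity is not threatened: selection alone leaves type I error at 4.5% to 5.5%.

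The size is moderate. If the effect is 61% vs 41%, power is already above 90% and the gain is small. If the 20% is relative, power is only about half and the gain matters more. Inflation arises only if the better of two answers is reported, and it is modest. These figures rest on 136 women per arm and on the assumed prevalence, independence and strength of the predictors; weaker predictors would give smaller gains. The change is worth making because it costs almost nothing.

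**What to change.** 1. Delete the baseline significance tests and keep the descriptive table by arm.
2. Before unblinding, fix one logistic model for epidural use with arm, parity (nulliparous or parous) and baseline preference for analgesia. Centre is optional, since no stratification by centre is stated. Use only values recorded before randomisation; leave out later events such as induction, which is itself a secondary outcome.
3. State which of the adjusted model and the Chi-squared comparison is primary, and report the other as a sensitivity analysis. Either choice is defensible; leaving it open is not.
4. Derive the adjusted risk difference, risk ratio and number needed to treat from the model by standardisation, with 95% confidence intervals, so that they match the measures the plan reports.

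**Cost:** wording and slightly more analysis work; no new data. One check is needed. The article places baseline collection at enrolment and says entry details are recorded before randomisation, but does not say that preference is among those details. Because the women are not blinded, confirm that it was recorded before allocation was known.

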### Objectives

The main objective of this study of women with uncomplicated pregnancies is to compare a standard antenatal care program with a program of aquatic-aerobic exercises of moderate intensity on the use of epidural analgesia during labor. The secondary objectives are to test the effect of the water exercise program on use of epidural analgesia before 6-cm cervical dilation, dystocic delivery, induction of labor, subjective satisfaction with the experience of childbirth, pain perception during the first stage of labor, duration of labor (first and second stages), and postpartum depression, and to assess the safety and cost-effectiveness of the aquatic-aerobic exercise program.

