### Edinburgh postnatal depression scale (EPDS)

The EPDS is a questionnaire originally developed to assist in identifying possible symptoms of depression in women during the postnatal period. It also has adequate sensitivity and specificity for identification of depressive symptoms in the antenatal period, and is useful in identifying symptoms of anxiety. The Spanish language version of the EPDS has been validated [45].

This study will also collect data on health resource utilization and pregnancy outcome, and will record and compare the rates of pregnancy complications and perinatal outcomes in the two groups. The latter will be obtained (with informed consent) from the existing computerized obstetric database and include:

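### Postpartum depression is assigned only a Chi-squared test; comparing the EPDS score alongside it would recover a material share of the information at almost no cost

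*Protocol article*

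**What the plan says.** The Objectives section of the protocol article lists among the secondary objectives "duration of labor (first and second stages), and postpartum depression". The section on the EPDS introduces the instrument: "The EPDS is a questionnaire originally developed to assist in identifying possible symptoms of depression in women during the postnatal period". It also credits the scale, for antenatal use, with "adequate sensitivity and specificity for identification of depressive symptoms". No cut-off, score range, SD or expected prevalence is given.

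The Statistical analysis section groups this outcome with modes of delivery: "post-partum depression, will be evaluated by a Chi-squared test". The next sentence treats the other scale outcome differently: "We will use the Mann-Whitney U test to determine if there is a statistically significant reduction of pain during labor using a VAS". The general rule is "All tests will be two-sided, and an α-value of 0.05 will be considered statistically significant". The article describes no analysis of the EPDS score itself.

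**The concern.** A Chi-squared test needs a categorical outcome, so the EPDS total has to be reduced to above or below a threshold. All differences among women on the same side of the threshold then drop out of the comparison. Instrumental and Caesarean delivery are yes/no by nature and lose nothing under this test. A questionnaire total does. The plan shows with the pain VAS that it is ready to analyse a scale as a scale, and it gives no reason for treating the EPDS otherwise.

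What is at stake is the reading of one secondary outcome. The Discussion section expects economic savings partly from less postpartum depression. If the yes/no comparison is the only one made, a moderate real benefit could well give a non-significant result and be reported as no difference, although the data already collected could have shown it.

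**Working it through.** **Inputs from the protocol article.** 160 women per group and an expected follow-up loss of 15% (Sample size); two-sided α of 0.05 (Statistical analysis). Evaluable women per arm: 160 × (1 − 0.15) = 136. The article states no figure of its own for the EPDS or for depression, so there is nothing to reproduce on this outcome. The 160 per group was set for epidural use.

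**Assumptions, not in the documents.** A control-arm share *p* above the cut-off of 10% to 20%, with 50% as the limiting case; a normal score with a uniform shift; then, as a check, one skewed score.

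**Step 1: information kept by the split.** For a small uniform shift of a normal score, the efficiency of the dichotomy relative to a comparison of means is φ(z)² / [p(1 − p)], where z is the normal quantile that leaves *p* in the upper tail.

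| p | φ(z)² / [p(1 − p)] | Lost against comparison of means | Lost against Mann-Whitney |
|---|---|---|---|
| 10% | 0.342 | 66% | 64% |
| 15% | 0.426 | 57% | 55% |
| 20% | 0.490 | 51% | 49% |
| 30% | 0.576 | 42% | 40% |
| 50% | 0.637 | 36% | 33% |

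The last column divides the efficiency by 3/π, the efficiency of Mann-Whitney itself for a normal score. The 50% split is the best case, so 36% (33% against Mann-Whitney) is the smallest loss under normality. The loss passes one half only when *p* is below about 21% (about 19% against Mann-Whitney).

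**Step 2: power with 136 per arm.** The shift with 80% power on the score is (1.960 + 0.842) × √(2/136) = 0.34 SD. The same shift applied to the yes/no outcome gives:

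| Control share | Share after the shift | Chi-squared power | Per arm for 80% power |
|---|---|---|---|
| 10% | 5.2% | 31% | 489 |
| 15% | 8.4% | 39% | 377 |
| 20% | 11.9% | 45% | 318 |
| 50% | 36.7% | 60% | 217 |

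Worked for 15%: the difference is 0.0656 and the pooled share 0.1172. The null SD term is √(2 × 0.1172 × 0.8828) = 0.455, and the alternative SD term is √(0.1500 × 0.8500 + 0.0844 × 0.9156) = 0.453. Power is Φ[(0.0656 × √136 − 1.96 × 0.455) / 0.453] = Φ(−0.28) = 0.39.

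**Step 3: sensitivity to shape.** A simulation used a rounded gamma score with assumed mean 6.5 and SD 4.5, a proportional drop of 1.5 points in the mean, and 136 per arm. Efficiency was taken as the ratio of (z of power + 1.96)².

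| Control share | Power, t-test | Power, Mann-Whitney | Power, yes/no | Lost against t-test | Lost against Mann-Whitney |
|---|---|---|---|---|---|
| 26% | 0.88 | 0.82 | 0.69 | 38% | 27% |
| 21% | 0.87 | 0.81 | 0.67 | 40% | 30% |
| 16% | 0.88 | 0.82 | 0.64 | 46% | 35% |
| 10% | 0.87 | 0.80 | 0.52 | 57% | 49% |

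The loss is smaller here because a proportional drop moves the upper tail more than the centre. It is still material in every row.

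**The case against.** The strongest reply is that the yes/no outcome answers the stated question. The objective names a condition, the EPDS is described in the language of case identification, and the savings foreseen in the Discussion most naturally mean fewer cases. A small shift among women far below any threshold is not less depression. Pain intensity has no case definition, so a different test for the VAS is not a contradiction. The trial was sized for the primary outcome and promises no power for this one. All of this stands. It is why the Chi-squared result should stay, and why putting the mean score in its place as the main analysis would be a debatable change of question.

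A second reply is that the article condenses a fuller document: its sentence on secondary measures gives examples, and a score analysis or a cut-off may be specified elsewhere. That stands too. The point therefore rests on the test that the article names, and the absence of a cut-off is not part of it.

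A reader might infer that the split always discards more than half the information, or nearly all differences between women. The documents do not support either. The first needs a roughly normal score and fewer than about 21% of women above the cut-off, and the article gives neither shape nor prevalence. In the skewed example the loss against Mann-Whitney stayed below half throughout. The second does not fit efficiencies of 34% to 49%. Eligibility requires no psychiatric problems, which makes a low share plausible but does not fix it.

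**Conclusion.** The concern holds as a matter of efficiency in one secondary outcome. The only test that the article names for postpartum depression reduces a scored questionnaire to yes/no. For a normal score with a uniform shift, that loses at least 36% of the information, and about 51% to 66% if 10% to 20% of women are above the cut-off. At 136 per arm, a shift of 0.34 SD has 80% power on the score and about 31% to 45% as yes/no under that assumed range. With a skewed score the loss can be smaller: 27% to 57% in the one example run, depending on the share above the cut-off and the comparator. If benefit is concentrated among high-scoring women, the disadvantage of the split also shrinks. Nothing in the plan is misstated, and the primary analysis is untouched. This is an optional but cheap improvement.

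**What to change.** Keep the Chi-squared comparison of the proportions above one cut-off, fixed before unblinding, as the case-based result. Pre-specify beside it a between-arm comparison of the postnatal EPDS total score by a single method chosen in advance, not by the skewness observed. Mann-Whitney U would match the VAS, reported with an estimated difference and its 95% CI. Adjust for an antenatal EPDS only if one is recorded: the article ties the EPDS to no particular visit and lists none at baseline. If adjustment is wanted, the method fixed in advance should be a regression on the score.

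The cost is one further analysis of data already collected, with no extra visit. The downside is two results for one secondary outcome, so the role of each must be stated in advance to prevent selective emphasis.

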### Follow up of women and infants

Midwifes will be responsible for data collection from the clinical history and from the questionnaires in all follow-up visits at gestation times of 17, 27, and 37 weeks. One month after birth, a follow-up visit will be used to assess maternal well-being, satisfaction with care, use of breast feeding, and early infant complications. Resource utilization and delivery of information regarding birth and infant outcomes will be obtained from the woman’s and infant’s case notes by the local research coordinator.

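### The ICER and its bootstrap are specified on arm means with no adjustment for starting EQ-5D, which gives up precision and leaves chance imbalance at entry in the QALY difference

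*Protocol article*

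**What the plan says.** The economic analysis is in the Statistical analysis section of the protocol article. It plans "calculating the incremental cost-effectiveness ratio (ICER) at 4 weeks from delivery". For the effect, "the EQ-5D scores will be used, and quality-adjusted life years (QALYs) will be determined". The estimator is given in words and as a formula with barred means: "The ICER will be calculated as the difference in the mean costs of the 2 groups", "divided by difference in the mean effects of the 2 groups". For uncertainty, "A nonparametric bootstrap procedure will be used to perform the uncertainty analysis for the ICER". The section then adds: "To control for possible confounding and to account for clustering, an alternative procedure (Net-Benefit Regression) will also be used". Acceptability curves are mentioned after that. No covariate is named for the ICER, the bootstrap or the regression.

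On timing, the Follow up of women and infants section has midwives collecting data "from the questionnaires in all follow-up visits at gestation times of 17, 27, and 37 weeks", with a further visit one month after birth. It does not say which instruments are used at which visit. Under Baseline data collection, "baseline demographic and medical information will be collected from all medical records at the time of enrollment"; the items listed there do not include EQ-5D. Recruitment is at 14 to 20 weeks of gestation.

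**The concern.** A QALY over the trial period is usually the area under each woman's utility scores, and the starting score is then its first point. A chance difference between arms at entry enters the QALY difference twice: mechanically, through the weight of that first point, and again because women who start higher tend to stay higher. A ratio of raw mean differences leaves both parts in the denominator.

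The horizon, from entry to four weeks after birth, is only about half a year, so QALY differences of a few thousandths are on the scale of the estimate's own standard error. Starting utility is likely to be the strongest available predictor of the QALY, and the allocation described (1:1, blocks of six) does nothing to balance it. What is at stake is the width of the ICER's uncertainty, and how far one realised estimate is displaced by the draw at randomisation.

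**Working it through.** **Figure to reproduce.** There is none. The only sizing figure in the article is 160 women per group, for epidural use. It gives no EQ-5D SD, correlation, QALY rule or expected QALY difference. What follows is an illustration.

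**Inputs from the article.** 160 per group and 15% loss, so 160 × 0.85 = 136 per arm. Visits at 17, 27 and 37 weeks and one month after birth.

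**Assumed.** EQ-5D is taken at all four visits. Birth is at 40 weeks, so the last score falls at about week 44. The 17-week score stands in for the starting score. QALY is by the trapezoid rule. SD is 0.15 at every visit, with equal correlation r between any two visits.

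**Step 1, weights.** The gaps are 10, 10 and 7 weeks. The trapezoid weights are 5, 10, 8.5 and 3.5 weeks, which sum to 27. Divided by 52 they are 0.0962, 0.1923, 0.1635 and 0.0673 years, with total W = 0.5192. The sum of squared weights is 0.0775.

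**Step 2, formulas.**
- Variance of one woman's QALY in units of SD²: V = (1 − r) × 0.0775 + r × W².
- Slope of the QALY on the starting score: b = 0.0962 + r × (0.5192 − 0.0962).
- Share of QALY variance explained by the starting score: R² = b² / V.
- Raw SE of the arm difference: SD × √(2V / 136).
- Adjusted SE: raw SE × √(1 − R²).

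**Step 3, worked at r = 0.5.** V = 0.0387 + 0.1348 = 0.1735. b = 0.3077. R² = 0.3077² / 0.1735 = 0.546. Raw SE = 0.15 × √(2 × 0.1735 / 136) = 0.0076. Adjusted SE = 0.0076 × √0.454 = 0.0051.

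**Step 4, range of r.**

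| r | b | R² (variance cut) | SE cut | Raw SE | Adjusted SE |
|---|---|---|---|---|---|
| 0 | 0.096 | 12% | 6% | 0.00506 | 0.00475 |
| 0.3 | 0.223 | 37% | about 20% | 0.00669 | 0.00531 |
| 0.5 | 0.308 | 55% | 33% | 0.00758 | 0.00511 |

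The gain at r = 0 is purely mechanical: the starting score is part of the QALY.

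**Step 5, range of SD.** The percentage cuts do not depend on the SD; the SEs scale with it. At r = 0.5 the SE goes from 0.0051 to 0.0034 with SD 0.10, and from 0.0101 to 0.0068 with SD 0.20.

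**Step 6, size of a chance imbalance.** With SD 0.15, the starting difference between arms has SE 0.15 × √(2 / 136) = 0.018. At r = 0.5, an imbalance of one such SE moves the raw QALY difference by 0.308 × 0.018 = 0.0056, about three-quarters of that difference's own SE of 0.0076.

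**The case against.** The strongest reply is that adjustment is already planned. The net-benefit regression is a covariate-adjusted cost-effectiveness analysis, the acceptability curves are mentioned straight after it, and a condensed article may leave its covariate list to a fuller plan. The formula could also be read as the generic definition of an ICER. Part of this stands. It would be wrong to infer that the economic analysis has no adjustment, or that the acceptability curves must be unadjusted; the article does not say which analysis the curves come from. But the estimator is written out as a ratio of differences in arm means and the bootstrap is applied to it. The regression is an additional alternative, so that ICER remains unadjusted as written.

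A second reply is that the trial is randomised and the bootstrap already expresses chance variation. This also stands. A reader might infer that the ICER would be biased, or would reflect the allocation draw more than the programme. The documents do not support either: the raw QALY difference is unbiased on average, and no expected QALY difference is given against which to judge an imbalance or a change of sign. Nor can a gain in power be claimed, since the article plans no test of QALYs and gives no power for one.

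A third reply is that the covariate may not exist. EQ-5D is not in the baseline list. A woman who enters at 14 weeks may have started classes before the 17-week visit, while for one who enters at 20 weeks that visit would precede enrolment. This stands, and it conditions the fix.

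**Conclusion.** The point holds as an efficiency improvement to a secondary analysis. The ICER and its bootstrap are specified without adjustment for starting utility, and the alternative regression neither changes that ICER nor names the covariate. Naming it would be expected to reduce the variance of the QALY difference by 12% to 55% for between-visit correlations from 0 to 0.5, and to remove the part of a chance imbalance that the starting score predicts. These sizes rest on the assumed EQ-5D schedule, trapezoid rule and equal correlations; the absolute SEs also rest on the assumed SD and on 136 women per arm. The direction does not depend on the particular values, provided that a starting score is part of the QALY. The epidural outcome is untouched.

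**What to change.** State in the economic analysis that the QALY difference is estimated by regression of QALY on arm and the EQ-5D score taken before the first class. Fit this within every bootstrap replicate, jointly with the cost difference, so that the covariance of costs and QALYs is kept. Prespecify the same covariate in the net-benefit regression, whether or not an imbalance is seen. Show the raw-mean ICER as a secondary line.

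The analysis cost is one sentence and one covariate, with three conditions:
- Confirm that EQ-5D is recorded before the first class. If it is not, collecting it at enrolment is an added data item for women still to be recruited.
- Do not use a score taken after classes have begun as the covariate, because the programme may already have affected it. This applies to the 17-week score for women who entered early.
- Fill in missing entry scores by simple imputation, for example the overall mean ignoring arm, so that no randomised woman is dropped for lack of the covariate.
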